#### Secondary outcomes

The secondary outcomes will be assessed according to the following measurements:*Gestational weight gain.* GWG will be measured at baseline and 36-week visit will be measured by trained staff with Wedderburn WM301 scales with 0.1 kg accuracy, in light clothing without shoes. Height will be measured on a calibrated stadiometer. Skin fold thickness measurements (biceps, triceps, subscapular) and arm circumference will be measured by trained staff according to a previously published protocol [48].*Nutrition intake*. Quality of diet will be measured by a previously published food frequency questionnaire [49].*Physical activity level*. Physical activity level will be assessed by the Pregnancy Physical Activity Questionnaire (PPAQ) [50]. Physical activity knowledge will be measured with previously published questions [51].*Theoretical behaviour change constructs*:*Knowledge*. GWG, nutrition and physical activity knowledge will be measured by previously utilised questions [51].*Attitude to GWG*. Attitudes toward GWG are measured by the Pregnancy Weight Gain and Attitude Scale [52] with modification.*Self-efficacy*. Self-efficacy for GWG, healthy eating and physical activity will be assessed with measures adapted from a self-efficacy scale for pregnant women [53].*Acceptability of intervention*. Participant questionnaire on acceptability and satisfaction with the intervention. Acceptability of each intervention component and suggestions for improvement will be measured through participant self-report Likert scales.

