### Trial entry

Eligible women will be identified at their first hospital antenatal visit to a university affiliated maternity hospital in Melbourne, Australia. Inclusion criteria are women with a singleton, live gestation between 10^+0^ and 17^+6^ weeks who have a self-reported pre-pregnancy, body mass index (BMI) > 25 kg/m^2^ and own a mobile phone. Exclusion criteria include: < 18 years of age; multiple pregnancy; comorbidities requiring significant medical and dietary management; discontinuation of care at hospital; or insufficient English to understand the intervention.

Eligible women will receive an introduction to the study by a researcher, and they will be provided with a plain language statement before obtaining informed consent.

One hundred women will be randomised, following consent, to the intervention or control group in a 1:1 ratio. The randomisation sequence will be obtained using a computer random number generator by JW. Randomisation will occur using numbered cards allocating women to either the intervention or control placed in opaque, sequentially numbered envelopes. Given the nature of the intervention participants will be aware of the group assignment.

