### Outcome measures

The primary outcome of intervention feasibility will be measured with programme metrics and participant reported data. The secondary outcomes concerning GWG, nutrition, physical activity and behavioural self-efficacy will assessed with self-reported and anthropometric data at baseline and 36 weeks gestation (Figure 1).

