### Statistical analysis

Analyses will be conducted using Stata (Release 12; StataCorp, College Station, TX, USA). The initial analysis will describe characteristics of participants at baseline. For feasibility assessment categorical variables will be reported as numbers and percentages and continuous variables as mean and standard deviation. Generalised Linear Models [54] will be used to examine intervention effects on the secondary outcomes. Sub-group analysis based on BMI categories will be performed for weight gain per week, and the proportion of participants exceeding IOM guidelines. Results will be analysed by the principle of ‘intention to treat’. The outcome assessors will be blinded to participant allocation.

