## Discussion

This paper presents an RCT protocol to determine the feasibility of an mHealth intervention to promote healthy nutrition, physical activity and weight gain in pregnant women who were overweight or obese prior to pregnancy. Previous authors have called for high-quality RCTs promoting healthy GWG grounded in health behaviour theoretical frameworks with adequate sample sizes and feasibility for translation to public health settings [15,23]. If effective, this mHealth intervention offers a programme that could be delivered for large numbers of pregnant women.

Small-scale RCTs that most closely approximate the clinical or community context of a larger-scale RCT help determine whether the intervention should progress to efficacy testing and offer high acceptability to participants and delivery agents, and high internal validity [34]. Given that future intervention success depends on the acceptability of the delivery modality to the target group, and their providers of care, the intervention model and elements of the model require consumer testing to ensure resonance and relevance.

This feasibility study has been designed to provide unique data regarding the suitability of an mHealth-delivered intervention to promote healthy diet, activity and weight in pregnant women. Results of comparisons will help assess relevance, applicability and feasibility of the programme. A potential limitation of the study is the reliance on the self-reported pre-pregnancy weight and nutrition intake and physical activity measures with the potential for recall bias, and hence, biased analyses. This is a common concern for GWG, nutrition and physical activity studies but given the purpose, size and budget of this study, more detailed assessments were not considered feasible. Importantly, the study strengths include the use of multiple technological elements to appeal to a range of preferences and learning styles and the potential for sustainable provision within models of antenatal care.

Findings will inform the development of larger-scale digitally-based programmes to improve the delivery of healthy pregnancy nutrition, physical activity and healthy GWG. The findings of this trial will contribute to the literature on promotion of healthy lifestyles in pregnant women.

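### If gestational weight gain is counted from the baseline visit, it spans 18 to 26 weeks depending on entry; allowing for this costs nothing and would modestly sharpen the arm comparison and the planning SD

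*Protocol article*

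**What the plan says.** All of this is in the protocol article.

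- **Entry.** Under Trial entry, eligible women have a "singleton, live gestation between 10^+0^ and 17^+6^ weeks".
- **Timing of assessment.** Under Outcome measures, the secondary outcomes use "self-reported and anthropometric data at baseline and 36 weeks gestation".
- **Weighing.** Under Secondary outcomes, "GWG will be measured at baseline and 36-week visit will be measured by trained staff with Wedderburn WM301 scales". The sentence says when and how women are weighed. It does not say which weight the gain is counted from.
- **Analysis.** Under Statistical analysis, "Generalised Linear Models [54] will be used to examine intervention effects on the secondary outcomes". No covariates are listed and none are ruled out. The next sentence reads "Sub-group analysis based on BMI categories will be performed for weight gain per week, and the proportion of participants exceeding IOM guidelines". This is the only mention of a gain per unit of time.
- **Reference weight.** The Discussion gives as a limitation the "reliance on the self-reported pre-pregnancy weight and nutrition intake and physical activity measures with the potential for recall bias, and hence, biased analyses".
- **Purpose.** The Sample size section gives estimating the SD of GWG as one reason for recruiting 100 women. It assumes an SD of 5 kg, a 3-kg difference and 10% dropout.

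**The concern.** Total gain from a baseline visit to a fixed gestational week is not the same quantity for every woman when the baseline visit can fall anywhere in a range of nearly eight weeks. A woman who enters early has longer to gain weight than one who enters late, whatever her arm. Part of the spread in the outcome then reflects recruitment timing and not weight behaviour.

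Two things are at stake. The arm comparison carries avoidable noise, including whatever imbalance in entry timing arises by chance. And the SD handed on to the larger trial includes a component set by this pilot's entry distribution, so it carries over less cleanly to a trial with a different entry rule. The plan already has a measure that allows for window length but ties it only to the BMI sub-groups.

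**Working it through.** **The plan's own figure.** With a 3-kg difference, SD 5 kg, two-sided 5% (sidedness assumed) and 80% power, the normal formula gives n per arm = 2 × (1.96 + 0.84)² × 25 / 9, which rounds up to 44. Dividing by 0.9 gives 49 per arm, 98 in total. The t-test version gives 45 per arm, 50 after dropout and 100 in total, an exact match. Power with 45 completers per arm is 81.2% (normal) or 80.4% (t). The sample size is not in dispute.

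**Window length, if gain runs from baseline.**
- Earliest entry: 36 − 10 = 26.0 weeks.
- Latest entry: 36 − 17.857 = 18.14 weeks.
- Spread: 7.857 weeks. Ratio: 26.0 / 18.14 = 1.43.

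**Contribution to the variance and to the arm difference.** The document gives no weekly rate of gain, so 0.3 to 0.5 kg per week is assumed. Entry is assumed uniform over the window, so the SD of window length is 7.857 / √12 = 2.27 weeks. Completers are 45 per arm.
- SD due to timing = rate × 2.27.
- Variance share = (SD due to timing)² / 25.
- 95% chance imbalance = 1.96 × SD due to timing × √(2/45).
- Residual SD = √(25 − (SD due to timing)²).

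| Assumed rate (kg/week) | SD due to timing (kg) | Variance share | 95% chance imbalance (kg) | Residual SD (kg) | Power at 45 per arm, adjusted |
|---|---|---|---|---|---|
| 0.3 | 0.68 | 1.9% | ±0.28 | 4.95 | 81.9% |
| 0.4 | 0.91 | 3.3% | ±0.37 | 4.92 | 82.5% |
| 0.5 | 1.13 | 5.1% | ±0.47 | 4.87 | 83.2% |

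**Sensitivity.** Widening the rate to 0.2 to 0.6 kg per week gives a variance share of 0.8 to 7.4% and a chance imbalance of ±0.19 to ±0.56 kg. In an extreme case, with half the women entering at each end of the window, the chance imbalance over that range is ±0.32 to ±0.97 kg.

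**Baseline value for the questionnaire outcomes.** Compared with analysing the 36-week value alone, adjusting for a baseline value with correlation r lowers the residual variance by the fraction r². For an assumed r of 0.4 to 0.7 this is 0.4² = 16% to 0.7² = 49%. Compared with analysing change scores, the reduction is (1 − r)/2, or 30% at r = 0.4 and 15% at r = 0.7. The document gives no correlations, so these figures are only illustrative.

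**The case against.** **A journal article need not list covariates.** This stands. A generalised linear model can take baseline value and gestational age as covariates, and the article rules neither out. A reader might infer that the analysis will be unadjusted, but the text supports only that no adjustment is stated.

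**The window may not apply.** The Discussion names self-reported pre-pregnancy weight as a source of bias, so gain may be counted from that weight. Entry timing would then not set the window. The remark could equally concern the BMI used for eligibility and sub-groups, which is also self-reported. The document does not settle which, so the 18-to-26-week figure is conditional.

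**Gain per week is already planned.** This is partly right. Naming it for sub-groups does not exclude an overall analysis, but nothing commits to one.

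**The effect is small.** This stands too. With about 90 completers, the 95% interval for an SD of 5 kg is roughly 4.4 to 5.9 kg, far wider than the shift from 5 to between 4.95 and 4.87 kg. If the larger trial keeps the same entry window and analyses total gain unadjusted, the raw SD is a proper planning value. GWG is also a secondary outcome of a feasibility pilot, and no primary conclusion depends on it.

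What remains is that the improvement is specific and free, and that it serves a stated purpose of the trial.

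**Conclusion.** The point holds as a no-cost improvement in precision and definition, not as an error that biases the result. It is conditional on gain being counted from the measured baseline weight. On that reading, with uniform entry and an assumed 0.3 to 0.5 kg per week, unequal windows account for about 2 to 5% of the assumed variance and a 95% chance imbalance of about 0.3 to 0.5 kg between arms.

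A reader might infer that recruitment timing alone could produce a shift as large as the 3-kg target. The documents do not support this. Two women at opposite ends of the entry window would differ by 7.857 × 0.3 to 0.5 = 2.4 to 3.9 kg at the same weekly rate, but that is a contrast between individuals, while 3 kg is a difference between arm means. Randomisation makes the expected timing difference between arms zero. Even in the most extreme case above, a 3-kg shift lies about 6 standard errors away.

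Nor does every other secondary outcome have an unused baseline value: acceptability of the intervention is listed among them and cannot be measured before the intervention starts.

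**What to change.** 1. State the weight from which GWG is counted, and reconcile the Secondary outcomes text with the Discussion on measured baseline weight versus self-reported pre-pregnancy weight.
2. For all randomised women with the outcome, model 36-week weight on arm with baseline weight, gestational age at baseline and gestational age at the final weighing as covariates. With baseline weight in an identity-link linear model, using GWG as the response gives the same arm estimate. Gestational age at the final weighing is recorded after randomisation, but it follows a scheduled visit; a check that it is similar between arms is enough.
3. Report weight gain per week for the whole trial as well as by BMI category.
4. Report the residual SD from this model beside the raw SD, so that the larger trial can use whichever matches its own entry window and analysis.
5. For diet, physical activity, knowledge, attitude and self-efficacy, include the baseline value of the same measure. Leave acceptability out of this.

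The cost is analysis wording only. Recruitment is complete, but nothing new has to be collected: gestational age at entry is needed for eligibility, gestational age at the final weighing follows from the visit date, and the baseline weights and questionnaires are already part of the schedule.

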### Statistical analysis

Analyses will be conducted using Stata (Release 12; StataCorp, College Station, TX, USA). The initial analysis will describe characteristics of participants at baseline. For feasibility assessment categorical variables will be reported as numbers and percentages and continuous variables as mean and standard deviation. Generalised Linear Models [54] will be used to examine intervention effects on the secondary outcomes. Sub-group analysis based on BMI categories will be performed for weight gain per week, and the proportion of participants exceeding IOM guidelines. Results will be analysed by the principle of ‘intention to treat’. The outcome assessors will be blinded to participant allocation.

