### Sample size

The primary outcome of this study is the assessment of feasibility. A sample of 100 participants allows for the estimation of the standard deviation of GWG, a continuous variable, and will give reliable data on the critical recruitment parameters for planning of a larger intervention trial [38]. While the study will not be adequately powered to detect GWG differences between groups, the sample is comparable in size to that of previous GWG studies [39,40] and will provide 80% power with an alpha of 5% to detect a 3-kg difference in GWG (secondary outcome) between the 2 groups, assuming a standard deviation of GWG of 5 kg and allowing for a 10% drop out.

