### Text messages

Individually-tailored, interactive text messages will be the core component of the intervention. To standardise the participant texting contact the texting schedule will commence from 16 weeks gestation. Participants will receive four to five texts per week. These texts will deliver information specific to women’s gestational week, encouragement of positive health behaviours and individual behaviour change, monitoring of individual goals and encouragement of self-monitoring of GWG. The text messages were informed by formative work and published data [46] and will be delivered using a two-way text messaging platform, developed by author BF in partnership with a commercial software developer. The package of 121 texts are informed by the CALO-RE taxonomy of behaviour change techniques [44] and delivered in the following categories and frequencies:Gestational progress (weekly)Information and behaviour change direction (twice weekly)Weight self-monitoring (weekly or fortnightly)Weight reporting (monthly)Individual goal checking (weekly or fortnightly)

In keeping with the suggestion that tailoring and personalisation of mHealth programmes encourages behaviour change [31] the text messages are tailored to participant’s gestational week, name and behaviour goal. Text schedules are also tailored to participant’s preferred frequency of self-monitoring and goal checking (for example, weekly or fortnightly) and time of day (for example, early or late morning). Two-way texting is used for the goal checking and weight reporting, which requires participants to respond to the message triggering an automated tailored response from the software. The texting component links participants to the website and Facebook® page.

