### Facebook®

Interaction with other participants is encouraged via access to a private Facebook® chat page only accessible by individual invitation. Moderated by a dietitian, participants can pose questions to health professionals and fellow participants as well as report their progress. The dietitian will answer questions within 48 hours and upload tips and information regarding healthy nutrition, physical activity and weight gain at least once per week. Intervention participants are encouraged to join this group during the initial interview with help offered if not proficient with Facebook®.

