### Participant incentives

All participants (n = 100) will be provided with a $20 voucher for completing each the initial and the final evaluations. Intervention participants (n = 50) will also be given a $20 iTunes® (Apple Inc., Cupertino, CA, USA) voucher at the initial interview to cover the cost of any text and Internet use.

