#### Primary outcome

The primary outcome of the intervention feasibility will be measured by a composite of programme metrics and participant self-reports. This process evaluation framework is informed by the Process-Evaluation Plan for Assessing Health Programme Implementation [47] and the eCONSORT guidelines [36].*Recruitment and retention*. Proportion of those who are assessed as eligible, those screened and those recruited and randomised. Extent of time taken to recruit. Proportion completing the study and providing evaluation data.*Intervention delivery and fidelity*. Successful intervention delivery to protocol as measure by system reports (delivered text messages, web analytics), and technological difficulties such as downtimes and unexpected events. Contamination of intervention with self-report of other services utilised.*Dose delivered and engagement in the intervention*. Metrics of use of each component: for example, web analytics for page views, time on individual pages, duration of visits, intensity of use, replies to messages, visits to website, views of and contributions to use of Facebook® chat forum. Participant questionnaire will also include participant reported usage of the different components of the intervention.

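### Mean and SD are the only summary fixed for continuous feasibility variables; for usage metrics they can overstate typical use and cannot show how many women used nothing

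*Protocol article*

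**What the plan says.** The Primary outcome section of the protocol article defines feasibility broadly: "The primary outcome of the intervention feasibility will be measured by a composite of programme metrics and participant self-reports". One of its three domains, dose delivered and engagement, lists "web analytics for page views, time on individual pages, duration of visits, intensity of use, replies to messages, visits to website" and also Facebook forum views and contributions. A questionnaire on use of each component supplements these.

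The Statistical analysis section then states: "For feasibility assessment categorical variables will be reported as numbers and percentages and continuous variables as mean and standard deviation". It attaches no condition on distribution and names no median or quartiles. It does not say which usage metrics count as continuous and which as categorical. Apart from a general intention-to-treat statement, this is the only analysis rule given for the primary outcome.

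The components differ in how use arises. Texts are scheduled: "Participants will receive four to five texts per week". The forum is optional: "Intervention participants are encouraged to join this group during the initial interview". The texts link women to the website, but no amount of website use is required.

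**The concern.** Page views, visit durations, website visits and forum contributions cannot fall below zero. Where use is voluntary, some women may never use a component and a few may use it heavily. The mean then sits above what the typical woman did, and the SD describes a spread that is not symmetric.

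The Discussion of the article says the findings will inform larger programmes, so readers will judge each component largely from the reported summary. A component used a lot by a few and not at all by many is a different feasibility result from one used moderately by most. The prescribed summary may not separate the two.

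**Working it through.** **1. The plan's own figure.** The only computed figure in the article is the sample size, which "will provide 80% power with an alpha of 5% to detect a 3-kg difference in GWG (secondary outcome) between the 2 groups", with SD 5 kg and 10% dropout. Taking alpha as two-sided:

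- n per arm = 2(1.960 + 0.842)² × 5² / 3² = 43.6, rounded up to 44.
- Allowing for dropout: 44 / 0.9 = 48.9, rounded up to 49 per arm, or 98 in total against the stated 100.
- With 45 evaluable women per arm, power is 81.2% (normal approximation) or 80.4% (t-test).

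The figure reproduces. The present point does not touch it.

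**2. Inputs for the summary statistic.** Participant incentives gives 50 intervention women, who supply the engagement data. The article gives no share of non-users and no skewness. Both are therefore assumed below and shown over a range.

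**3. Mean and SD cannot identify non-use.** Suppose half the women have 0 uses and half have 10. The mean is 5 and the SD is √(½·5² + ½·5²) = 5. An exponential distribution with mean 5 also has SD 5 and has no non-users. The same reported pair therefore fits 50% non-use and 0% non-use.

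**4. Mean against median, closed form.** Assume 30% non-users and log-normal use among the rest, with median 1 and log-SD s.

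- Mean = 0.7·exp(s²/2).
- Median = exp(s·z), where z = Φ⁻¹(0.2/0.7) = −0.566.
- s = 0.8: 0.964 / 0.636 = 1.5.
- s = 1.2: 1.438 / 0.507 = 2.8.
- s = 1.5: 2.156 / 0.428 = 5.0.

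**5. Mean against median at n = 50.** This uses 20,000 simulated samples with a median of 5 among users. The table gives the average of the sample means and the middle value of the sample medians and SDs.

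| Non-users | log-SD | Mean | Median | SD | Mean / median |
|---|---|---|---|---|---|
| 0% | 0.5 | 5.66 | 5.01 | 2.89 | 1.13 |
| 20% | 0.5 | 4.53 | 4.27 | 3.42 | 1.06 |
| 0% | 1.0 | 8.26 | 5.01 | 8.93 | 1.65 |
| 20% | 1.0 | 6.60 | 3.65 | 8.45 | 1.81 |
| 40% | 1.0 | 4.94 | 1.88 | 7.58 | 2.63 |
| 40% | 1.5 | 9.23 | 1.20 | 18.47 | 7.69 |
| 60% | 1.0 | 3.30 | 0 | 6.27 | not defined |

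**6. Counter-case.** Replies are capped by the number of prompts sent. For a reply rate distributed as Beta(4,1), the mean is 4/5 = 80% and the median is 0.5^(1/4) = 84%, so the mean is slightly too low. For Beta(2,2) both are 50%.

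**The case against.** A reader might infer that the usage metrics are skewed and zero-heavy, that the primary outcome will therefore overstate engagement, and that the website or forum could be carried forward wrongly. The article does not support this. It reports no usage distribution, the gap can be small, and it can reverse for reply rates. It also sets no numeric engagement threshold that an inflated mean could meet, so no wrong decision can be shown.

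Further objections stand:

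- The mean is a legitimate measure of average dose, which belongs to the named domain.
- The same sentence allows numbers and percentages for categorical variables, so any use could be reported as a proportion. Questionnaires on usage and acceptability add information.
- An SD larger than the mean would itself warn of skew.
- The article does not say that web analytics are recorded per woman, and the Website section describes no individual login. Without per-woman records, a per-woman median cannot be computed.
- Time taken to recruit is a recruitment measure with no non-users. It does not belong in this point.

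It can also be said that medians are routine detail that an article leaves to a fuller document. That would answer a complaint of silence, but here the article states a rule for the primary outcome. It permits any-use percentages without committing to them, and a large SD signals skew without giving the share of non-users.

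**Conclusion.** The point holds as a reporting weakness in the primary outcome. Mean and SD are the only summary fixed for continuous feasibility variables, and some of these are counts or durations from components that women may leave unused. For such metrics the mean can overstate typical use. That mean and SD cannot reveal the number of non-users follows without any assumption about the true distribution.

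The size of any overstatement is unknown from the article. Under the assumed distributions it runs from about 6% to more than seven-fold, with a positive mean against a median of zero when 60% do not use a component, and a slight reversal for bounded reply rates. The optional forum and self-initiated website use make zeros and right skew plausible, but do not establish them.

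**What to change.** Amend the sentence on feasibility summaries in the Statistical analysis section as follows:

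- For each usage metric recorded per woman, report median, quartiles and range alongside mean and SD.
- For each component, report the number and percentage of all randomised intervention women with any use, and count non-users as zero in the usage metrics.
- Where web analytics exist only for the whole site, report them as totals and take any use from the participant questionnaire.

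A measure of sustained use is optional.

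The cost is a sentence or two and slightly longer tables. Engagement may look less favourable. Recruitment is complete, but only reporting changes. The wording should be settled before the usage data are summarised.
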